#### 8.2.2 Assessment and Documentation of Adverse Events

Monitoring of relevant clinical and laboratory safety parameters will be undertaken by researchers at the time of each visit.

Any adverse event will be assessed and managed by the participant's physician, or general practitioner, with the event followed to resolution. Conditions that are present at screening and do not deteriorate will not be considered adverse events. Abnormal laboratory values will not be adverse events unless deemed clinically significant by the investigator and documented as such. Changes in the severity of an adverse event will be reported. Adverse events characterised as intermittent will be documented for each episode. All adverse events will be followed to adequate resolution, where possible.

Any serious adverse event will be reported in writing to the relevant HREC within 72 hours of the event. The description of each adverse event on the CRF will include:

- A description of the adverse event;
- The onset date, duration, date of resolution;
- Severity (mild, moderate or severe);
- Seriousness (i.e. is it an SAE?)
- Any action taken (e.g. treatment, follow-up tests);
- The outcome (recovery, death, continuing, worsening);
- The likelihood of the relationship of the adverse event to the study treatment (unrelated, possible, probable, definite).

The seriousness of an adverse event will be assessed by an investigator according to the definition stated above in this section, with the following exception:

Hospitalisation due to progression of disease will not be considered a serious adverse event for the purpose of this study.

Adverse events due to the study (rather than the clinical procedure) are not expected to occur. Where study results suggest patterns of adverse events related to clinical care, study personnel will discuss concerns with clinical teams in a timely manner.

An oversight committee will be responsible for the on-going monitoring of reports of serious adverse events (SAEs) as well as data relating to psychological outcome questionnaires. This committee will consist of independent clinical monitors, a statistician and trial investigator (non-voting role). They will be responsible for identifying safety concerns and make recommendations to the Trial Steering Committee for continuing or stopping the trial. The trial will be stopped if >5% participants overall are withdrawn by investigators for safety reasons related to the intervention. This will include any significant adverse events (SAEs) that occur.

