### ***Phase 3: Step down diet intervention (weeks 17–52)***

Participants in both the experimental arm (IER) and active control arm (standard hypocaloric diet) will continue with the prescribed intervention during this phase. The dietitian will review dietary intake and weight loss at each visit, modify goals as necessary, and encourage adherence to the intervention. During this phase, participants will have less contact with the study dietitian than in previous phases. Participants will meet with the dietitian at week 52 (end of study). At weeks 20, 26 and 36 the contact will be either face-to-face, by phone or electronically using Zoom, Skype,

Facetime or telehealth platforms approved by the health facility. A minimum of two contacts will be face-to-face during this time. Additional dietitian support will be provided via text message, phone or email at weeks 18, 24, 28, 42 and 48.

COVID 19: During the pandemic face to face visits will only be undertaken as directed by the health facility, and participants are able to meet with the study dietitian at weeks 20, 26 and 36 electronically using Zoom, Skype, Facetime or telehealth platforms approved by the health facility.

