### 7.2.6 Contingency plans

At each clinical visit, the investigator (or delegate) will determine whether any AEs have occurred. Adverse events will be recorded in the AE page of the eCRF. If known, the medical diagnosis of an AE should be recorded in preference to the listing of individual signs and symptoms. The investigator must follow up on the course of an AE until resolution or stabilisation. If an AE is ongoing after the end of study visit, the AE will continue to be followed up until resolution or stabilisation.

If, during the study period, a participant presents with a pre-existing condition that was not noted at the time of study entry, the condition should be retrospectively recorded in the Medical History section of the eCRF. For SAEs occurring during the study, the investigator or delegate will enter all relevant information in the AE page of the eCRF. AEs due to this low risk study are not expected to occur; none were observed in the pilot study. Where study results suggest patterns of adverse events, study investigators will discuss concerns with clinical teams in a timely manner.

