### 7.6.2 Retention strategies

Strategies to retain participants in the study include:

- Thank you, birthday and Christmas/ New Year greetings.
- Facility for updating contact details and recording details of two family members or close friends.
- SMS reminders for appointments.

We will also provide:

- Some flexibility in scheduling appointments.
- At least weekly contact between the study team and participants offering a variety of contact methods including face-to-face meetings, Skype, face-time, zoom, telehealth appointments, telephone calls, emails, or SMS text messages, depending on the participants preference.
- Timely feedback on healthy lifestyle changes and weight goals using a practical, supportive and flexible approach suited to this age group.
- Free parking (Monash) or parking vouchers (CHW) and a petrol gift card at each face-to-face visit to assist with travel costs.
- Gift Vouchers at 52 week appointments (\$20 Coles Myer gift card).
- Fitbit® wristbands (Fit Bit Flex 2) will be given to participants at week 16 to enhance motivation and engagement as contact with the dietitian decreases during the final phase of the study

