### **8.2.3 Eliciting Adverse Event Information**

All participants will be asked about any health related problems at each visit. Biochemical testing will occur as per the protocol. Adverse events will be recorded in case report forms.

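### The 72-hour SAE deadline runs from the event, while events are described as asked about only at visits up to 16 weeks apart; the clock should run from staff awareness

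*Protocol*

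**What the plan says.** On the deadline, protocol section 8.2.2 reads: "Any serious adverse event will be reported in writing to the relevant HREC within 72 hours of the event". The period is counted from the event.

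On how events come to light, three places point to visits:

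- Section 7.2.6: "At each clinical visit, the investigator (or delegate) will determine whether any AEs have occurred".
- Section 8.2.2: "Monitoring of relevant clinical and laboratory safety parameters will be undertaken by researchers at the time of each visit".
- Section 8.2.3: "All participants will be asked about any health related problems at each visit".

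The table under section 7.1 puts the Phase 3 dietitian consults at weeks 20, 26, 36 and 52. Between them, section 7.2.2 (Phase 3) schedules lighter contacts: "Additional dietitian support will be provided via text message, phone or email at weeks 18, 24, 28, 42 and 48". Section 7.6.2 lists, as a retention strategy, "At least weekly contact between the study team and participants offering a variety of contact methods". None of these lighter contacts is given a role in asking about adverse events.

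On recording, section 7.2.6 says: "For SAEs occurring during the study, the investigator or delegate will enter all relevant information in the AE page of the eCRF". It sets no time limit. Section 8.2.2 also gives an oversight committee the task of monitoring SAE reports, again with no time limit for those reports to reach it.

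**The concern.** A reporting deadline can bind staff only from the moment they know of the event. Here the clock starts earlier, at onset, and the described way of learning about events is a question at visits that become sparse in Phase 3. For an SAE that the family does not volunteer, the 72 hours will usually have run out before anyone on the study team can act. The document gives no second clock, counted from awareness, for that case.

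The stake is timely safety information on minors following an energy-restricted diet that, by the protocol's own account, has not been studied in a published adolescent trial. An inpatient admission meets the protocol's SAE definition. One found eight weeks later would simply be recorded as late, with nothing to say how soon the HREC or the oversight committee must then hear of it. The primary outcome and its analysis are not affected.

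**Working it through.** The 72 hours is a rule, not a computed figure, so there is nothing to reproduce. The check compares the visit spacing with the deadline.

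**Inputs.** Deadline: 72 hours = 3 days from the event (8.2.2). Consult weeks from the end of Phase 1: 4, 6, 9, 12, 16, 20, 26, 36, 52 (table under 7.1). Phase 3 support contacts: weeks 18, 24, 28, 42, 48 (7.1 and 7.2.2).

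**Assumptions.** The event is not volunteered. Its onset is uniform over the interval. Every consult takes place on schedule and counts as a visit. The written report is filed the day the event is found. The last two favour the protocol: the week 20, 26 and 36 consults may be by phone or video, and a missed visit lengthens the gap.

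**Step 1: gaps between consults in Phase 3.** From week 16: 20−16 = 4, 26−20 = 6, 36−26 = 10, 52−36 = 16 weeks. The longest is 16 × 7 = 112 days = 2,688 hours, about 37 times the 72-hour limit.

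**Step 2: share of unvolunteered events found in time.** Within one gap of G days, only onset in the last 3 days can be met, so the share is 3/G.

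| Period | Consult gaps | Days | Found within 72 hours |
|---|---|---|---|
| Weeks 36–52 | 1 | 112 | 3/112 = 2.7% |
| Weeks 16–52 (Phase 3) | 4 | 252 | 12/252 = 4.8% |
| Weeks 4–52 | 8 | 336 | 24/336 = 7.1% |

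So in weeks 36 to 52, 109/112 = 97.3% of unvolunteered events are overdue at discovery.

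**Step 3: mean delay to discovery.** For one gap this is G/2; over several gaps it is ΣG²/(2ΣG).

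- Weeks 36–52, consults only: 16/2 = 8 weeks.
- All of Phase 3, consults only: (4² + 6² + 10² + 16²)/(2 × 36) = 408/72 = 5.7 weeks.

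**Step 4: the same with an SAE question at the support contacts.** The Phase 3 gaps become 2, 2, 4, 2, 2, 8, 6, 6, 4 weeks. The longest is now 8 weeks (week 28 to 36).

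- Weeks 36–52: (6² + 6² + 4²)/(2 × 16) = 88/32 = 2.75 weeks.
- All of Phase 3: (4 + 4 + 16 + 4 + 4 + 64 + 36 + 36 + 16)/72 = 184/72 = 2.6 weeks.

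These assume that the contact is answered.

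**Step 5: would more asking alone rescue the event-based clock?** No. With the support contacts included, the in-time share in weeks 36–52 rises only to 9/112 = 8.0%. Even a question every 7 days would catch 3/7 = 43% in time. The start of the clock has to change; the added question does a separate job, which is to shorten detection.

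**The case against.** The strongest reply is that this is a drafting matter. The protocol says that participants are asked at visits; it does not say that this is the only route. Besides the contacts already mentioned, section 7.2.2 provides weekly texts, an optional app for messaging dietitians and closed social media groups, and families may well report a hospital admission on their own. The calculation covers only events that nobody volunteers, and the documents give no basis for saying how large that group is. The session checklists and information sheets are listed in the appendix but not shown, and may already ask about events or tell families to report them. All of this stands, and it limits the point to unvolunteered events and to what the body text states. It does not remove the mismatch: no between-visit route has a stated adverse-event role, and none starts a clock at awareness.

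A reader might infer three stronger things that the documents do not support:

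- That the rule is breached by design. It is not: an SAE volunteered promptly, or arising within 72 hours before a visit, can be reported in time.
- That late-found SAEs have no working deadline and escape reporting. They do not: the duty covers any SAE, so a late one is overdue, not exempt.
- That the stopping rule depends on the 72-hour report. Section 8.2.2 ties stopping to the percentage of participants withdrawn by investigators for safety reasons. Late knowledge of an SAE could delay such a withdrawal, but the rule has no 72-hour element.

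It may also be said that once the clock is corrected, the extra question is optional. It is not needed to make the deadline achievable. But an awareness clock alone would make late discovery compliant without making it any earlier.

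**Conclusion.** The point holds in limited form, and it is minor. The clock in section 8.2.2 does not fit the visit-based detection described in 7.2.6, 8.2.2 and 8.2.3. For unvolunteered SAEs the deadline has usually passed at discovery: about 97% in weeks 36 to 52 and about 93% (1 − 24/336) over weeks 4 to 52. This rests on uniform onset and consults kept on schedule. How many SAEs would go unvolunteered is unknown, so these are shares of that subset and not of all SAEs. The firm finding, which needs no assumption about timing, is that the text contains no reporting deadline counted from awareness.

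**What to change.** 1. In section 8.2.2, run the 72 hours from the time study staff become aware of the SAE, and apply the same clock to reports to the oversight committee.
2. In section 8.2.3, add one standard SAE question, in both arms, to the support contacts already scheduled at weeks 18, 24, 28, 42 and 48. If the session checklists already contain such a question, a reference to them is enough.

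The first change makes the stated rule achievable; the second brings the detection gain worked out above. The cost is two sentences in the protocol, a little more dietitian time and probably a few more recorded events. No visit is added and no outcome or analysis changes.

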## 5.3 Background information

### ***Increasing prevalence of obesity in adolescence, especially of severe obesity***

One in four Australian adolescents has overweight or obesity. In contrast to the situation in primary school-aged children, *prevalence rates in this age group have continued to increase* in recent years. Rates of severe obesity in adolescence have more than doubled in the past two decades [1].

Obesity in adolescence is often complicated by psychosocial distress and associated with a range of other health problems, including insulin resistance, orthopaedic disorders, high blood pressure, fatty liver disease, dyslipidaemia and type 2 diabetes [2, 3]. If untreated, obesity in adolescence is highly likely to persist into adulthood, with many attendant complications.

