## 7.7 Inclusion Criteria

- Adolescents aged 13–17 years (inclusive)
- Obesity (defined as equivalent to adult BMI 30–45 kg/m^2) [58] and at least one of the following metabolic complications:
  - o Pre diabetes: impaired fasting glucose 5.6-6.9mmol/L and/or impaired glucose tolerance 2 hour post load 7.8-11.1mmol/L
  - o Insulin resistance: fasting insulin (pmol/L)/glucose(mmol/L) ratio >20
  - o Presence of acanthosis nigricans
  - o Hypertension: systolic and/or diastolic blood pressure above the 90th percentile for sex, age and height
  - o Low HDL-C <1.03mmol/L
  - o High triglycerides ≥ 1.7mmol/L
  - o Abnormal Alanine Transaminase (ALT) or Gamma-Glutamyltransferase (GGT) based on standard PowerChart cut-points (i.e. ALT or GGT >45 U/L)
  - o Diagnosis of polycystic ovary syndrome (PCOS)

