### 8.2 Adverse Event Reporting

#### 8.2.1 Definitions

An adverse event is any undesirable sign, symptom or medical condition occurring after starting the study therapy (the IER diet). A medical condition/disease present before starting the study treatment will only be considered an adverse event if it worsens after starting the study treatment.

Pregnancy will be reported as an adverse event and followed to determine the outcome. Any study participant who becomes pregnant during the study will be withdrawn from the study.

A serious adverse event is an undesirable sign, symptom or medical condition which,

- (1) is fatal or life-threatening,
- (2) requires admission to hospital as an inpatient,
- (3) results in persistent or significant disability/incapacity,
- (4) constitutes a congenital anomaly or birth defect,
- (5) is medically significant, may jeopardize the participant and may require medical or surgical intervention to prevent one of the outcomes listed above.

A SUSAR is a serious adverse event that is suspected to be related to the study but unexpected.

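### The SAE exception for admissions due to disease progression has no defined scope, so an admission for worsening of an entry condition can bypass ethics committee and oversight reporting

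*Protocol*

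**What the plan says.** Section 8.2.1 lists five criteria for a serious adverse event. The second is that the event "requires admission to hospital as an inpatient". The same section says that a condition present before treatment "will only be considered an adverse event if it worsens after starting the study treatment". Worsening of a pre-existing condition is therefore an adverse event, and it becomes serious if it leads to admission.

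Section 8.2.2 hands the judgement to an investigator and qualifies it: "The seriousness of an adverse event will be assessed by an investigator according to the definition stated above in this section, with the following exception". The exception follows: "Hospitalisation due to progression of disease will not be considered a serious adverse event for the purpose of this study".

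Three safeguards in the protocol depend on SAE status:
- Section 8.2.2 requires a written report of any SAE to the HREC within 72 hours.
- Section 8.2.1 defines a SUSAR as a type of SAE.
- Section 8.2.2 gives the oversight committee SAE reports and psychological questionnaire data to monitor.

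Section 7.7 requires obesity "and at least one of the following metabolic complications". The list covers prediabetes, insulin resistance, acanthosis nigricans, hypertension, low HDL cholesterol, high triglycerides, abnormal ALT or GGT, and polycystic ovary syndrome.

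**The concern.** An exception for disease progression can be applied consistently only if the protocol names the disease and says what progression is. This protocol does neither, and there is more than one candidate. Obesity itself is one and each entry complication is another. Section 5.3 names further conditions that go with adolescent obesity: "insulin resistance, orthopaedic disorders, high blood pressure, fatty liver disease, dyslipidaemia and type 2 diabetes".

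The exception also acts before relatedness is considered. It turns on whether the admission is labelled as progression, not on whether the diet may have contributed. An admission that the investigator rates as probably related to the diet could still be exempt.

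Section 5.1 says that the study will test whether intermittent energy restriction is safe, and Section 5.2 describes it as the first randomised trial of this diet in adolescents. Deterioration that leads to admission is an event that an SAE listing in such a trial should show.

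**Working it through.** No figure in the protocol bears on this point, so the check is a reading of the rules side by side.

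**Step 1. Is the disease or its progression defined?** No. Section 8.2.2 uses the phrase once. The protocol gives no definition, no criteria and no adjudication step.

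**Step 2. Follow one case through the rules.** Take a participant who enters with prediabetes and is later admitted as an inpatient with newly diagnosed type 2 diabetes.

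| Question | Rule | Result |
|---|---|---|
| Is it an adverse event? | 8.2.1: a pre-existing condition has worsened | Yes |
| Is it serious under the definition? | 8.2.1, criterion 2: inpatient admission | Yes |
| Is it exempt? | 8.2.2: if the investigator calls it disease progression | It can be |
| Is it on the case report form, with relatedness? | 8.2.2 and 8.2.3: all adverse events | Yes |
| Does it go to the HREC within 72 hours? | 8.2.2: SAEs | No, if exempt |
| Can it be a SUSAR? | 8.2.1: must first be an SAE | No, if exempt |
| Is it in the oversight committee's SAE reports? | 8.2.2: SAEs | No, if exempt |

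The answers in the last three rows do not change if relatedness is rated possible, probable or definite.

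**Step 3. Does another criterion bring the event back?** It may. The exception concerns hospitalisation, which is criterion 2. It does not expressly switch off criterion 1 (fatal or life-threatening), criterion 3 (disability) or criterion 5 (medically significant). An admission that meets one of these may still be an SAE, although the text does not say so. The clear loss is an admission that is serious only because it is an admission.

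**Step 4. Are admissions captured as an outcome?** No. Hospital admission is not among the outcomes in Sections 6.3.1 and 6.3.2.

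**Step 5. Is the person who applies the exception blinded?** The protocol does not say. Section 7.4 blinds the assessors of the primary and secondary outcomes, and Section 9.3 says that the analysis will be blinded. Neither covers the investigator who judges seriousness.

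**The case against.** The strongest reply is that this is an open, stated carve-out and that little is lost. Much of that reply stands.

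- The event is still recorded. Section 8.2.2 requires description, severity, action taken, outcome and relatedness for every adverse event. What is lost is the SAE label and the reporting that depends on it.
- Worsening can be found by other routes. Section 8.2.2 has clinical and laboratory safety parameters monitored at each visit, glucose, insulin, lipids and liver function are scheduled outcomes, and Section 7.5 has a medical review at 16 weeks. These routes can detect a change in an individual, but they do not send an admission to the HREC or the oversight committee.
- No practical impact can be shown. The protocol gives no admission rate and does not suggest that the entry conditions often lead to admission.

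Two stronger readings are tempting, and the protocol does not support them.

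First, a reader might infer that the exception undermines the stopping rule. More than 5% of 186 is more than 0.05 × 186 = 9.3, or 10 participants, so each exempted admission could seem to remove a tenth of the trigger. But the rule in Section 8.2.2 counts participants whom investigators withdraw for safety reasons related to the intervention. It does not count admissions. A participant withdrawn for such a reason after an exempted admission still counts. The sentence that follows the rule, "This will include any significant adverse events (SAEs) that occur", is ambiguous and may mean only withdrawals that result from SAEs. The figure of 10 therefore does not measure this defect.

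Second, a reader might infer that SAEs will be classified differently in the two arms. Because no blinding is stated for the investigator, this is possible. Nothing in the protocol shows that it is likely, and the same gap applies to every adverse event judgement in the trial.

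**Conclusion.** The point holds as a defect in the safety reporting rules. Read as written, Section 8.2.2 lets an admission for worsening of an entry condition be recorded only as a non-serious adverse event. It then bypasses the 72-hour HREC report, SUSAR classification and the oversight committee's SAE review, whatever its relatedness rating. This is more than missing detail, because a stated rule removes events from escalation.

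The size cannot be given as a number. The conclusion rests on two assumptions: that an investigator could reasonably read disease as obesity or one of its complications, and that the admission meets no other seriousness criterion. The change should be made, because participants are minors, safety is a stated question of the trial and the correction costs little.

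**What to change.** Delete the exception and its lead-in from Section 8.2.2, so that the criteria in Section 8.2.1 apply without qualification. State that every inpatient admission for an adverse event, in either arm, is reported as an SAE. The words on both arms are needed because Section 8.2.1 ties adverse events to the start of the IER diet alone. The existing scale in Section 8.2.2 (unrelated, possible, probable, definite) then separates background illness from diet effects.

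The cost is a short protocol amendment and a few more SAE forms, some of them for admissions that prove unrelated.

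If the sponsor keeps an exception, the minimum is to define the disease and the progression meant, confirm that the other seriousness criteria still apply, and send exempted admissions to the oversight committee.

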## 5.2 Introduction

One in four Australian adolescents has overweight or obesity, with prevalence rates continuing to rise. Effective treatment of obesity in this age group is vital. Dietary interventions are generally effective in treating obesity in the short term, but the best way to achieve weight loss longer term in adolescents is unknown. Young people with obesity find it very difficult to adhere to the routine of daily calorie restriction - a core element of current weight management programs.

A new diet intervention that has demonstrated success in adults is intermittent energy restriction (IER), a variant of which is the diet popularised as the “5:2 Diet”. There are many variations of IER in the literature, approaches typically involve 2-6 days per week of intense energy restriction (i.e. consuming 25-35% of daily energy needs) alternated with days of healthy eating or ad libitum intake

Despite the current research interest in IER in adults, there have been no studies of its use in adolescents. There are potential safety concerns as to whether IER promotes the development of disordered eating and whether it is nutritionally adequate. However, the avoidance of every day calorie restriction, the overall lower energy intake that IER provides, and its flexibility in terms of youth lifestyles makes IER potentially very appealing, and hence sustainable to adolescents. This study is the first randomised controlled trial (RCT) of IER in adolescents.

This study is a multisite RCT weight-loss intervention comparing IER with a standard hypocaloric diet in adolescents aged 13-17 years with obesity.

The study *challenges existing clinical paradigms* by proposing that IER can be implemented as an alternative to standard continuous energy restricted diets for adolescents with obesity.

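### Section 8.2.2 does not say that the oversight committee receives the safety withdrawals counted by the >5% stopping rule, or non-serious adverse events

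*Protocol*

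**What the plan says.** The relevant text is the last paragraph of Protocol section 8.2.2. It names two data streams for the oversight committee, which is "responsible for the on-going monitoring of reports of serious adverse events (SAEs) as well as data relating to psychological outcome questionnaires". It then gives a wider duty: "They will be responsible for identifying safety concerns and make recommendations to the Trial Steering Committee for continuing or stopping the trial". Next comes the stopping rule: "The trial will be stopped if >5% participants overall are withdrawn by investigators for safety reasons related to the intervention". A further sentence adds: "This will include any significant adverse events (SAEs) that occur". The members are independent clinical monitors, a statistician, and one trial investigator without a vote.

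Other safety information is placed with trial staff. Earlier in 8.2.2: "Monitoring of relevant clinical and laboratory safety parameters will be undertaken by researchers at the time of each visit". Also in 8.2.2: "Where study results suggest patterns of adverse events related to clinical care, study personnel will discuss concerns with clinical teams in a timely manner". Section 7.2.6 (Contingency plans) has a similar sentence about study investigators, without the limit to clinical care. Under section 7.5 (Diet review), the study dietitian checks that the diet is adequate.

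Section 5.2 sets out what safety monitoring has to address: "There are potential safety concerns as to whether IER promotes the development of disordered eating and whether it is nutritionally adequate".

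**The concern.** The paragraph gives the committee a decision to advise on and a numerical rule for stopping, but its listed inputs do not include the quantity that the rule counts. Investigator withdrawals for safety are neither SAE reports nor questionnaire data. Section 8.3 (Handling of Withdrawals) does not mention reporting them to the committee. The list of attachments in section 12 includes no committee charter that might do so.

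Non-serious events have the same problem. The protocol describes the study as low risk and as the first randomised trial of this diet in adolescents, so any early signal may well lie below the SAE definition. As written, a pattern of such events goes from trial staff to clinical teams. No route is given to the body with independent members.

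At stake are whether the stopping rule can be applied reliably and on time, and whether a cluster of non-serious events would get an independent look. The primary analysis is not affected.

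**Working it through.** **1. The denominator.** Sections 7.2.1 and 9.1 give 186 participants, from 130 evaluable (section 9.2) and 30% attrition: 130 / (1 − 0.30) = 185.7, rounded up to 186. This reproduces.

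**2. The threshold as a count.** The rule is met at the smallest whole number above 0.05 × N. The protocol says only that the percentage is of participants overall, so N could be all randomised or those enrolled so far:

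| N taken as denominator | 0.05 × N | Withdrawals that meet the rule |
|---|---|---|
| 186 (all randomised) | 9.3 | 10 |
| 93 (half enrolled) | 4.65 | 5 |
| 50 (early in recruitment) | 2.5 | 3 |

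The values 93 and 50 are chosen for illustration. The trigger is a small count that depends on the denominator. Applying the rule therefore needs a running tally of investigator safety withdrawals and a stated N. No sentence says who keeps the tally, who receives it, or how often.

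**3. Listed inputs against what is needed.**

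| Item | Stated to reach the committee? | Where the protocol places it |
|---|---|---|
| SAEs | Yes | 8.2.2; also reported to the ethics committee within 72 hours |
| Psychological questionnaires (disordered eating) | Yes | 8.2.2 |
| Investigator safety withdrawals | Not stated | 8.3, no reporting route |
| Non-serious adverse events | Not stated | Study personnel and investigators, 8.2.2 and 7.2.6 |
| Clinical and laboratory safety parameters | Not stated | Researchers at each visit, 8.2.2 |
| Dietary adequacy | Not stated | Study dietitian, 7.5 |

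**4. The two named safety concerns.** The questionnaires cover disordered eating. Nutritional adequacy is covered by no listed input unless a problem is serious enough to be an SAE.

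**5. Whether adverse events can be compared by arm.** Section 8.2.1 defines an adverse event by its onset after starting the study therapy, which it identifies as the IER diet. Read literally, that does not clearly cover the control arm. Section 8.2.3, however, has all participants asked about health problems at each visit. The definition and the collection need to agree before any by-arm table is meaningful.

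**The case against.** The strongest reply is that much of this is silence, not exclusion. The text does not say that the committee sees nothing else. Its duty to identify safety concerns is unrestricted, the stopping rule follows that duty directly, and a trial investigator sits on the committee. Receipt of withdrawal counts may be implied, or set out in terms of reference not shown here. This stands as far as it goes: a reader might infer that the committee is denied these data, and the protocol does not say so. But two streams are spelled out and the others are assigned to trial staff, so the wording needs reconciling.

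A reader might also infer that the committee cannot tell at all whether its own threshold has been crossed. Two points count against that. The rule is said to include SAEs, which the committee monitors, although it is unclear whether SAEs count in themselves or only as reasons for withdrawal. And the rule is not expressly the committee's: no body is named as applying it.

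The sentence in 8.2.2 on patterns of adverse events concerns those related to clinical care, so it is not a general rule for all events. Section 7.2.6 is broader, though discussing a pattern with clinical teams does not bar telling the committee.

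Three stronger claims are not supported:

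- **Laboratory results would reveal nutritional inadequacy.** Section 5.3 names calcium, iron and zinc, but the follow-up panel in 7.5 is hs-CRP, lipids, glucose, insulin and liver function. It lists no nutrient marker. The protocol manages nutrition by other means: modelled meal plans, a multivitamin and dietitian review.
- **The committee should routinely see height and weight change by arm.** To week 52 that is in substance the primary outcome, BMI z-score at 52 weeks. It would be shown to a committee that includes a trial investigator, while section 9.3 calls for blinded analysis.
- **Non-serious events would detect a difference that SAEs would miss by some stated margin of power.** The protocol gives no event rates, and section 7.2.6 reports no adverse events in the pilot. Any such contrast depends on the rates chosen.

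**Conclusion.** The point holds as a mismatch within section 8.2.2. The remit lists two data streams, while the stopping rule in the same paragraph turns on a third that is not stated to reach the committee. The rule would be met at 10 withdrawals if the denominator is all 186 randomised, and at fewer if it is those enrolled so far. Neither the denominator nor the body applying the rule is stated. Non-serious adverse events are likewise not stated to reach the committee.

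The gap is partial. SAEs and questionnaire data do reach the committee, and a nutritional or growth problem that met the SAE definition would too. A reader might conclude that nutritional adequacy has no independent monitoring whatever; the text supports this only below the SAE threshold.

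The conclusion rests on the wording of 8.2.2, 7.2.6 and 8.3 and assumes no charter that fills the gap. It does not depend on assumed event rates. An amendment is worthwhile because the data are already collected and the change is small.

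**What to change.** Amend section 8.2.2 so that the remit and the stopping rule agree:

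- State that the committee receives a running count of investigator withdrawals for intervention-related safety reasons, with its denominator defined.
- State that it receives all adverse events by severity, including laboratory values judged clinically significant.
- Present both by coded arm, in a session closed to the trial investigator.
- Name the body that applies the >5% rule, and clarify how SAEs enter it.

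Amend section 8.2.1 so that adverse events are defined and captured alike in both arms. Without this the by-arm table could mislead.

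Do not add a routine by-arm report of weight change.

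The cost is a few sentences of text, a slightly longer committee report and a closed session. No new data and no extra participant visits are needed. This change does not provide a measure of nutritional adequacy; it only ensures that related adverse events below the SAE threshold reach the committee.
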